## Abstract

**Background:**

The management of acute febrile illnesses places a heavy burden on clinical services in many low- and middle-income countries (LMICs). Bacterial and viral aetiologies of acute fevers are often clinically indistinguishable and, in the absence of diagnostic tests, the ‘just-in-case’ use of antibiotics by many health workers has become common practice, which has an impact on drug-resistant infections.

Our study aims to answer the following question: in patients with undifferentiated febrile illness presenting to outpatient clinics/peripheral health centres in LMICs, can we demonstrate an improvement in clinical outcomes and reduce unnecessary antibiotic prescription over current practice by using a combination of simple, accurate diagnostic tests, clinical algorithms, and training and communication (intervention package)?

**Methods:**

We designed a randomized, controlled clinical trial to evaluate the impact of our intervention package on clinical outcomes and antibiotic prescription rates in acute febrile illnesses. Available, point-of-care, pathogen-specific and non-pathogen specific (host markers), rapid diagnostic tests (RDTs) included in the intervention package were selected based on pre-defined criteria. Nine clinical study sites in six countries (Burkina Faso, Ghana, India, Myanmar, Nepal and Uganda), which represent heterogeneous outpatient care settings, were selected. We considered the expected seasonal variations in the incidence of acute febrile illnesses across all the sites by ensuring a recruitment period of 12 months. A master protocol was developed and adapted for country-specific ethical submissions. Diagnostic algorithms and choice of RDTs acknowledged current data on aetiologies of acute febrile illnesses in each country. We included a qualitative evaluation of drivers and/or deterrents of uptake of new diagnostics and antibiotic use for acute febrile illnesses. Sample size estimations were based on historical site data of antibiotic prescription practices for malarial and non-malarial acute fevers. Overall, 9 semi-independent studies will enrol a minimum of 21,876 patients and an aggregate data meta-analysis will be conducted on completion.

**Discussion:**

This study is expected to generate vital evidence needed to inform policy decisions on the role of rapid diagnostic tests in the clinical management of acute febrile illnesses, with a view to controlling the rise of antimicrobial resistance in LMICs.

**Trial registration:**

Clinicaltrials.gov NCT04081051. Registered on 6 September 2019. Protocol version 1.4 dated 20 December 2019

## Background

The World Health Organization (WHO) considers antimicrobial resistance (AMR) to be ‘an increasingly serious threat to global public health that requires action across all government sectors and society’ [1]. It is estimated that 700,000 deaths each year are due to drug-resistant pathogens; by 2050, if no actions are taken to contain AMR, this figure is predicted to rise to 10 million deaths per year [2].

Inappropriate self-treatment and ‘just-in-case’ antibiotic prescribing practices, along with inadequate doses and treatment duration, are considered the 5main contributing causes of AMR [3, 4]. Optimizing the use of antimicrobial agents is one of the four pillars of the WHO Global Action Plan on AMR [5]. However, identifying the causative agent of an infection, or at least distinguishing between bacterial and viral infections, remains a challenge, as few diagnostics are suited to this task and are not yet affordable for widespread use in low- and middle-income countries (LMICs). Most health facilities in LMICs lack the diagnostic capacity to correctly identify the cause of an acute febrile illness, thus undermining a health worker’s ability to determine whether an antibiotic is required or not [6]. To this end, an adaptation in prescription practices needs to occur to improve patient management by healthcare staff and to change patient behaviours as well as treatment-seeking behaviours. Success will mean making significant steps toward achieving the dual goal of tackling AMR and providing universal health coverage (UHC).

Recent work in LMICs has focused on unravelling the diverse aetiologies of acute febrile illnesses especially in children [7–13]. Data from outpatient settings are scarce, with a small number of studies describing the relative distribution of bacterial, parasitic and viral agents among acutely febrile patients [7]. These diagnoses often rely on complicated serological and/or nucleic acid detection assays which are not available in primary healthcare centres, where many ill patients first present for care. Currently, there is a lack of quality-assured point-of-care tests (POCTs) for many infectious causes of fever in LMICs. Moreover, even when regulatory-approved POCTs are available, there is, in many instances, a paucity of data on their clinical usefulness within the operational contexts found in these settings [14].

WHO, in its recent technical consultation on in vitro diagnostics for AMR, has stressed the need for research and development on additional tests that can distinguish between bacterial and non-bacterial infections at primary healthcare facilities. In order to be fit for purpose, such POCTs should be rapid diagnostic tests (RDTs) such as lateral-flow tests or easy-to-use, robust diagnostic platforms that use accessible, minimally invasive clinical specimens (e.g. whole blood, urine stool or nasal swabs) [15].

Practical solutions, adapted to LMICs, are needed to provide better healthcare to patients presenting with fever, allowing healthcare workers to confidently prescribe, or not prescribe, an antibiotic based on the evidence of test results. These solutions must be applicable now, with existing tools, but also be amenable to incorporate newer and better tools, when they become available.

In recent times, attempts have been made to build antimicrobial stewardship programs into the healthcare landscape in LMICs to correct inappropriate antimicrobial prescribing and use practices [16]. This cannot happen without a proper understanding of the bacteria that are causing disease in the different countries, of how to use currently available diagnostic tests and to incorporate these tests into clinical diagnostic algorithms and how to modify practices and behaviours in order to correct ineffective management of acute febrile illnesses. The most appropriate platform for evaluating such interventions are research centres that are firmly integrated within the health system, have access to clinical care facilities and have a platform for population-based evaluation of immediate and long-term impact.

This is the basis for the intervention research study described below. All the diagnostic tests described have regulatory approval and are commercially available, but have never been field-tested together, as part of decision-making algorithms for use in peripheral health facilities in LMICs.

This study is part of the FIND AMR Diagnostics Use Accelerator, a platform which intends to stimulate studies to investigate the outcome of innovative clinical algorithms using existing diagnostic kits and to inform research into the design and implementation of effective behavioural change interventions. The project comes at an opportune time for institutions with the appropriate capacity to integrate diagnostics into healthcare delivery and to appropriately evaluate the impact.

### Study objectives

This study aims to address the following question that is based on the PICO process [17]:

In children and adolescents (+/− adults) who present to outpatient clinics or peripheral health centres in LMICs with acute febrile illness (Population), will introducing a package of available diagnostic tests, diagnostic algorithms, new clinic process flows, and training and communication for healthcare workers and patients or caregivers (Intervention), as compared with current practice (Control), improve case management of acute febrile illnesses and better target the correct use of antibiotics (Outcome)?
Primary study objectives: to assess the impact of a package consisting of diagnostic tools, clinical algorithms, and training and communication on (1) clinical outcomes and (2) antibiotic prescriptions, compared with routine practices for children and adolescents (+/− adults in certain sites—see Table 1) presenting at outpatient clinics.Secondary study objectives: to assess adherence (1) to the new diagnostic algorithm by healthcare workers, (2) to prescriptions by patients/caregivers, and (3) to evaluate the safety outcomes of these practices.

**Table 1 Tab1:** List of clinical trial sites, their locations and age ranges of participants

Country	Uganda	Nepal	Myanmar	Ghana	Burkina Faso	India			
Institution	Infectious Diseases Research Collaboration (IDRC)	Oxford University Clinical Research Unit-Nepal	Myanmar Oxford Clinical Research Unit (MOCRU) and Medical Action Myanmar (MAM)	Dodowa Health Research Centre	IRSS-DRCO/Clinical Research Unit of Nanoro (CRUN)	Chhattisgarh: Jan Swasthya Sahyog (JSS)	Chandigarh: Post Graduate Institute of Medical Education & Research (PGIMER)	Madhya Pradesh: RD Gardi medical college	West Bengal: National Institute for Cholera and Enteric Diseases (NICED)
Number of recruiting sites	3	1	4	2	2	4	1	1	2
Nature of recruiting sites	Health centres in three regions (two rural and one peri-urban) with varied geography and malaria endemicity, outside Kampala	Large, urban teaching hospital in Kathmandu	NGO supported, stand-alone clinics located in peri-urban areas, and one hospital in Yangon	one regional referral hospital in greater Accra, and one rural hospital	Rural, health centres 90 km from the capital	Rural health centres	Teaching hospital for urban and rural patients	Urban medical college	Small clinics located in urban slums in Kolkata
Age ranges included	all ages > 1 year	all ages > 6 months	all ages > 1 year	6 months to 18 years	6 months to 18 years	6 months to 18 years	all ages > 6 months	all ages > 3 months	6 months to 18 years

### Explanation for choice of comparators

For this programmatic study, routine clinic processes will serve as the comparator to the intervention package. However, different to routine practice, both arms will have a day 7 follow-up visit to the health facility.

## Design and methods

### Study settings

The study sites were identified through two calls for partners: one for Africa and Asia (excluding India) [18], and one for India only [19]. Applications were reviewed by two respective selection committees who recommended three sites in Africa, two in Asia and four in India; after appropriate due diligence the sites were chosen. Information on the sites is summarized in Table 1.

### Study design

The study design captures a wide range of qualitative contextual outcomes and quantitative empirical outcomes in order to address the various aspects of the core research question.

Overall, this is a prospective, comparative, multicountry and multisite, open-label, two-armed, 1:1, randomized-controlled trial which will compare the impact of the intervention package (POCTs, clinical algorithm, clinic process flow, and training and communication) on clinical outcomes and antibiotic prescription patterns in febrile patients with the current practice. All sites have adopted a common protocol that reflects differences in patterns of infection and behaviours at each site and in each geographical area.

As this is principally a site-level study, sample sizes have been generated to provide the required statistical power for each individual site. Analyses will be conducted at two levels: first at the site level on individually randomized study participants, and secondly, on the combined studies as an aggregated-data meta-analysis across all sites, with the site as the unit of analysis.

### Study participants

The study will recruit children and adolescents (and adults at some sites—Table 1) attending study site outpatient facilities who present with an acute febrile illness (current or within the past 7 days) defined as fever with no focus or suspected respiratory tract infection (RTI).

### Qualitative pre-intervention study

The qualitative study will be conducted to understand the contextual factors and behavioural determinants affecting adherence to prescriptions by patient/caregivers and the associated communication about prescriptions by healthcare workers. The findings will inform the Training and Communication package which will be implemented as part of the clinical intervention arm consisting of diagnostic algorithms, POCTs, prescribing decision trees, clinic process flow, training and communication on adherence to prescription. Further research using the capacity, opportunity and motivation (COM-B) model [20] together with the Theoretical Domains Framework (TDF) [21] during the recruitment phase will investigate the wider behaviour change implications of adherence to prescription beyond the Training and Communication package, as well as the long-term effects of behavioural determinants for healthcare workers who choose to use the clinical algorithms, new point-of-care RDTs and associated prescribing practices.

### Interventions

The trial intervention will consist of (1) diagnostic tests (Table 2), (2) diagnostic and clinical algorithm (Fig. 1), (3) training and communication of healthcare workers and patients/caregivers and (4) clinic process flow.

**Table 2 Tab2:** Pathogen-specific point-of-care (POC) tests

Pathogen	Type of test
Dengue virus	Lateral flow RDT: detects Dengue virus NS1 antigen and IgM (and IgG) from serum or whole blood
*Streptococcus pyogenes*	Lateral flow RDT: detects group A streptococcal antigen from throat swabs
*Salmonella enterica* serovar Typhi	Lateral flow RDT: detects *Salmonella typhi*-specific IgM from serum or whole blood
*Orientia tsutsugamushi* (scrub typhus)	Lateral flow RDT: detects *Orientia tsutsugamushi* antibodies (IgG, IgM, and IgA) in human serum, plasma, whole blood
Influenza virus	Lateral flow RDT: detects influenza virus type A, type B and A(H1N1) pandemic antigens directly from nasal/throat/nasopharyngeal swab or nasal/nasopharyngeal aspirate
Chikungunya virus	Lateral flow RDT: detects Chikungunya virus IgG/IgM antibodies in serum, plasma or whole blood
*Streptococcus pneumoniae*	Lateral flow RDT: detects *S. pneumoniae* antigen in the urine of patients with pneumococcal pneumonia
Respiratory syncytial virus	Lateral flow RDT: detects respiratory syncytial virus (RSV) fusion protein antigen in nasal wash and nasopharyngeal (NP) swab specimens
*Leptospira interrogans* (leptospirosis)	Lateral flow RDT: detects *Leptospira interrogans* IgM antibodies from urine
*Plasmodium Sp*. (malaria)	Lateral flow RDT as per national guidelines

**Fig. 1 Fig1:**
[figure not shown]
Outline of diagnostic and clinical algorithm. RSV, respiratory syncytial virus; GAS, group A streptococci; CRP, C-reactive protein; WBC/DIFF, white blood cells total counts/differential counts; Rx, treatment; ATB, antibiotic; Y, prescribe antibiotic; N, antibiotic prescription not warranted; P, antibiotic prescription possible if clinically indicated

#### Diagnostic tests

The diagnostic tests to be used in the intervention package (Table 2) will be selected based on local needs.

Non pathogen-specific POCTs:
White blood cell total and differential counts (WBC/diff)Urine dipstickC-reactive protein (CRP)

#### Diagnostic and clinical algorithm

Healthcare workers will follow a country-specific algorithm for cases in the intervention arm, which takes into account the specific tests to be used at the site. A typical clinical algorithm is outlined in Fig. 1. Notably, the decision on pathogen-specific diagnostic tests to use in each case was based on clinical presentation, which we have grouped into respiratory and non-respiratory signs and symptoms. In addition, clinical decisions in the intervention arm will be supported by CRP and WBC/diff POCT.

#### Training and Communication package

Communication messages about adherence to prescription are delivered by healthcare worker(s) to the study patient or caregiver in the intervention arm. The method of delivery of the communication message will be site-specific, depending on the roles of different types of healthcare workers, and behavioural determinants identified in the qualitative analysis. Training is provided to healthcare workers to deliver the communication messages; together, the training and delivery of the messages make up the Training and Communication package developed for each site based on findings from the qualitative work identifying behavioural drivers of adherence to prescriptions. The delivery of the core communication message will be personalized to the individual patient (e.g. adjusting emphasis, but not message content), based information collected from the patient before clinical assessment.

#### Clinic process flow

At the majority of sites, the clinic process flow described below, closely follows the normal clinic flow, only with minor changes to speed up the process, such as mechanisms to minimize queuing.

### Participant flow

The participant flow is shown in Fig. 2. Patients presenting at the clinic will be pre-screened for fever and those meeting the study eligibility criteria will be enrolled in either the control or intervention arm of the study by simple, 1:1 randomization. Participants in both arms will be seen by clinicians who will collect patient histories and conduct clinical examinations.

**Fig. 2 Fig2:**
[figure not shown]
Study participant flow

Patients in the control arm will follow routine diagnostic and treatment procedures for acute febrile illness as outlined in each clinic. Patients in the intervention arm will first be asked to provide information on their attitude towards the use of antibiotics, and then undergo a provisional diagnosis (respiratory/non-respiratory). Samples will be taken from patients to be performed using POCTs and any other tests based on the provisional diagnosis and algorithm. An additional communication package to influence adherence to prescription will be provided by the study team (clinicians, pharmacist and/or nurses) before the patient leaves the facility.

All patients in both the intervention and control arms will be followed up on day 7 (+/− 2) in the health facilities, to reassess their health status and prescription adherence.

Patients who do not improve following the day of enrolment will need to visit the health facilities making an unscheduled visit before the day 7 (+/− 2) follow-up visit for further assessment and management.

The package of POCTs provided in the intervention arm is considered to be an addition to tests provided in routine care. Therefore, where site routine protocols include the use of blood culture or other laboratory tests, these will also be conducted in the intervention arm (along with the normal practice in the control arm). Patients will return to the clinic for review of their prescription in light of these test results, following the normal schedule.

### Biological specimens

Biological samples will be handled as outlined below:
Two millilitres of venous blood samples will be taken from adult patients and children over 5 years of age, as per the Seattle Children’s Hospital Guidelines (no venous sample will be taken from patients weighing less than 4 kg and less than 5 years for safety reasons).For children under 5 years of age, finger prick blood will be taken instead of 2 mL venous blood. The blood sample will be used for PoC tests (CRP, Hb and white cell differential and pathogen specific rapid tests) as per clinical algorithms and SOPs adapted from product manufacturers’ user manuals.A nasopharyngeal swab will be taken from patients who need to be tested for influenza or respiratory syncytial virus or both as per clinical algorithm and SOPs adapted from product manufacturers’ user manuals.A throat swab will be taken from patients with pharyngitis/pharyngitis and tested as per clinical algorithm and SOPs adapted from product manufacturers’ user manualsA urine sample will be taken for patients with suspect of urinary tract infection or who need *Streptococcus pneumoniae* urine antigen tests (adults) and tests performed as per SOPs adapted from product manufacturers’ user manuals.Repeat or unscheduled samples may be taken for safety reasons or for technical issues with the samples.All unused samples will be destroyed according to national or site-specific sample destruction guidelines.No biological samples will be stored.

### Strategies to improve and assess adherence

Patients and caregivers in the intervention arm (but not the control arm) will receive a communication message in support of adherence to the prescription, based on the local research findings described above. The method of delivery of the communication message will be site-specific, depending on the roles of different types of healthcare workers, and the behavioural determinants identified in the qualitative analysis.

The delivery of the core communication message will be personalized to the individual patient (e.g. adjusting emphasis, but not message content), based on a small amount of information collected from the patient before clinical assessment.

All patients in both the intervention and control arms will be followed up on day 7 (+/− 2) in the health facilities to reassess their health status and adherence to prescription. Information on adherence to prescription will be collected using qualitative in-depth interviews with the patient and through pill counts (participants/caregivers will be asked to bring back packaging and remaining medicine on day 7). This includes assessing the behaviour of patients who were not prescribed medication to find out if they obtained any antibiotics or any other treatment, the reasons for this and where the antibiotics or other treatment were obtained.

All enrolled participants (and caregivers, in case of children) will be reminded prior to departure on day 0 to visit the health facilities if their illness worsens before day 7. All participants who do not return on day 7 will be followed up via telephone to assess their well-being and the need to return to the clinic for the end of study assessment. Where feasible and where consent was provided by study participants at enrolment, the investigators will conduct home visits if the patient is unable to return to the clinic for the day 7 follow-up visit.

Adherence to the diagnostic algorithm will be evaluated by reviewing the case report forms (CRFs) to assess algorithm-driven use of POCTs and antibiotic prescriptions.

### Study outcomes

The primary outcome measures are the point estimates of:
The proportion of cases of acute febrile illness with favourable outcome (defined as being alive + no fever + resolution of day 0 symptoms) on day 7, in both arms.The proportion of antibiotic prescriptions for acute febrile illness in the two arms. Specifically, the study intends to detect a reduction (at least 30% from the baseline) in unnecessary antibiotic prescribing, without adversely affecting clinical outcomes. While antibiotic prescription rates are known at the study sites, outcomes are not currently known because patients are not routinely followed-up.

The secondary outcomes are:
Proportion of patients prescribed antibiotics at clinics who describe adherence to prescription on day 7.Proportion of healthcare workers who adhered to new algorithm.Proportion of participants experiencing adverse events (see description in Safety reporting section).

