### Blinding and masking

Not applicable as this is an open label study.

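### The secondary adherence outcome is worded as self-report, although only the intervention arm is coached on adherence and pill counts are already planned in both arms

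*Protocol article*

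**What the plan says.** Under Study outcomes, the first secondary outcome is "Proportion of patients prescribed antibiotics at clinics who describe adherence to prescription on day 7". The line names no pill count, cut-off or comparison between arms.

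Under Strategies to improve and assess adherence, the article says "Patients and caregivers in the intervention arm (but not the control arm) will receive a communication message in support of adherence to the prescription". Participant flow gives the purpose and the source of that message: "An additional communication package to influence adherence to prescription will be provided by the study team".

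The same Strategies section describes the data. "All patients in both the intervention and control arms will be followed up on day 7", with a window of 2 days either side. "Information on adherence to prescription will be collected using qualitative in-depth interviews with the patient and through pill counts", and "participants/caregivers will be asked to bring back packaging and remaining medicine on day 7". For those who miss the visit, "All participants who do not return on day 7 will be followed up via telephone".

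The entry under Blinding and masking reads: "Not applicable as this is an open label study".

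**The concern.** Intervention patients are told by clinic staff on day 0 to follow their prescription. About a week later they are asked, normally at the same facility, whether they did. Control patients receive no such message. Coached patients who did not adhere therefore have more reason to say that they did. If that tendency differs by arm, described adherence differs by arm even when behaviour does not, and the error favours the intervention. A larger sample only makes the wrong difference more precise. Pooling sites would not average the error out if it runs the same way everywhere.

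Patient adherence to prescriptions is a stated secondary objective, and the Training and Communication package is built around it. A reader will naturally look to this outcome to see whether that component changed behaviour. The article plans a less subjective measure in both arms, but the outcome definition does not mention it.

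**Working it through.** The article states no adherence rate, target difference or power for this outcome, so there is no figure to reproduce. Its sample size rests on antibiotic prescribing alone. The check has two parts.

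**1. The passages side by side**

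- Outcome definition: what patients describe on day 7.
- Data planned: interview and pill count, in both arms.
- Adherence message: intervention arm only, from the study team.
- Masking: none.

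Nothing in the article says that the pill count enters the outcome, or which source prevails when interview and count disagree.

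**2. Size of the possible bias (assumed values, not document figures)**

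Let t be true adherence, equal in both arms, and let r be the share of non-adherent patients who describe themselves as adherent.

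- Described adherence = t + (1 − t) × r
- Spurious difference = (1 − t) × (r in intervention − r in control)

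Assume t = 60%, 70% or 80%, r = 30% in control, and r = 40% or 50% in intervention.

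Patients prescribed antibiotics come from Table 4: N per arm × the control rate, and × 0.7 again in the intervention arm for the targeted 30% reduction.

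- India JSS: 864 × 0.50 = 432 control; 432 × 0.7 ≈ 302 intervention.
- Burkina Faso: 859 × 0.77 ≈ 661 control; 661 × 0.7 ≈ 463 intervention.

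The last two columns give the chance of a false difference in favour of the intervention, were a two-sided 5% test of two proportions made (normal approximation).

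| True adherence | r in intervention | Described, control vs intervention | Spurious difference | India JSS | Burkina Faso |
|---|---|---|---|---|---|
| 60% | 40% | 72% vs 76% | 4 points | 22.5% | 32.1% |
| 60% | 50% | 72% vs 80% | 8 points | 70.1% | 87.0% |
| 70% | 40% | 79% vs 82% | 3 points | 16.7% | 23.4% |
| 70% | 50% | 79% vs 85% | 6 points | 54.1% | 72.7% |
| 80% | 40% | 86% vs 88% | 2 points | 11.8% | 16.0% |
| 80% | 50% | 86% vs 90% | 4 points | 36.4% | 51.9% |
| any | 30% | equal | 0 | 2.5% | 2.5% |

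Two rows in full, for India JSS at 70% true adherence:

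- r = 50%: 70 + 0.50 × 30 = 85% against 70 + 0.30 × 30 = 79%. SE = √(0.79 × 0.21/432 + 0.85 × 0.15/302) = 0.028, so 6 points is about 2.1 SE.
- r = 40%: 70 + 0.40 × 30 = 82% against 79%. SE = √(0.79 × 0.21/432 + 0.82 × 0.18/302) = 0.030, so 3 points is about 1 SE.

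The Table 4 numbers include the allowance for loss to follow-up. Dividing by 1.1 gives about 393 and 275 patients at India JSS, and the chance then runs from 11.1% to 65.9%. The result depends strongly on the assumed gap in over-reporting. It is small when that gap is small and vanishes when the gap is zero.

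**The case against.** The strongest reply is that the outcome line is only a label and the Strategies section is the operational text. That section collects pill counts in both arms, and nothing excludes them from the outcome. The full SAP, which the article says is under review, may combine the two sources. This stands in part: the article can be read as intending the count to inform adherence. But the outcome line does not say so, and applied literally it gives self-report. The two sections need aligning.

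Second, no between-arm test of adherence is stated. The primary outcomes name both arms and this one does not, and the Efficacy analyses section lists between-arm estimates only for clinical outcome and antibiotic use. This stands, so the bias matters only if adherence is compared between arms. A two-arm trial of a package that includes an adherence message invites that comparison.

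Third, the over-reporting rates are assumed. This stands, and it is why a range is given. A reader might infer from the 79% against 85% row that a falsely significant result is to be expected. The 79% against 82% row, at about 1 SE, shows that this does not follow.

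Fourth, pill counts are imperfect. Medicine can be discarded, packs may be returned selectively, and patients reached only by telephone have no count. The article does not say that the dispensed quantity is recorded. All of this stands: the count lessens the bias but does not abolish it.

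**Conclusion.** The concern holds in a limited form. As worded, the secondary adherence outcome is self-report, in an open-label trial that coaches one arm only, while a more objective measure is already planned in both arms. If arms are compared, differential over-reporting could produce a spurious 2 to 8 points in favour of the intervention. That range assumes equal true adherence of 60% to 80%, 30% over-reporting among non-adherent controls and 40% to 50% among non-adherent intervention patients.

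Three stronger readings are not supported:

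- A reader might infer that the compliant against non-compliant comparisons (Efficacy analyses, Analysis of endpoints, Other analyses) inherit the bias. The article does not define compliant there, and Table 5 speaks of compliance with the protocol, so they are affected only if they use the same measure.
- A reader might infer that the plan judges adherence against a finished course although the visit can fall on day 5 to 9. The article nowhere says so. The window matters only for how a count should be scored.
- A reader might infer that the primary results are at risk. Neither primary outcome is defined on adherence.

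Separately, the outcome covers only patients prescribed antibiotics, a group formed after randomisation that the intervention is meant to change. Better measurement does not make the arms comparable on that score.

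**What to change.** Reconcile Study outcomes with Strategies to improve and assess adherence:

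- Define the outcome on the pill count: (quantity dispensed − quantity returned) ÷ doses due by the actual visit date. Use the prescribed quantity where the dispensed quantity is not recorded.
- Set one cut-off before the data are seen and apply it alike in both arms.
- Report described adherence as supportive.
- Where no pack is returned or follow-up is by telephone only, flag the patient as self-report only.
- Show by arm the pack-return rate and the agreement between described and counted adherence.
- State that the restriction to patients prescribed antibiotics remains a limit on any between-arm comparison.

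The cost is a change of outcome wording and a derived variable. The pill counts are already planned; the one point to check is whether the dispensed quantity is captured. The downside is missing counts for patients who bring back no pack, which may differ by arm and so must be shown, and some bias will remain in the counts themselves.
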